## **2. OBJECTIVES OF THE STUDY**

This study has 3 objectives:

1. To determine if the proposed intervention will improve language outcomes.
2. To examine the immediate impact of aerobic exercise on cerebral circulation
3. To examine the neural mechanisms of sustained change in reading outcomes following the proposed intervention.

To address Objective 1, we will randomize 100 chronic (>3 months post-stroke) left hemisphere stroke participants to either the aerobic exercise (AET) or the stretching condition. The AET condition will complete 20 minutes of moderate intensity aerobic exercise in the form of stationary bike cycling prior to a 1.5-hour targeted reading treatment session using phono-motor therapy (PMT) (Kendall et al., 2019). The control condition will complete 20 minutes of light

stretching before each PMT session. Both conditions will also have a 5-min warm up and cold down. All participants will complete 40, 2-hour intervention sessions administered 3-5 times per week for 8-10 weeks. We will measure reading competence as the primary outcome, and naming, auditory comprehension, and spontaneous speech as secondary language outcomes using standardized and experimental tasks administered before and after the full course of treatment. We expect a condition by time interaction, such that the AET condition will improve more than the stretching condition from baseline to end of treatment.

To address Objective 2, we will ask participants to undergo 2 MRI scans, one at baseline and one following the first AET or stretching session. The scans will assess regional and whole brain cerebral blood flow and functional connectivity to determine the immediate impact of aerobic exercise vs. stretching on neural and vascular processes. A greater increase in cerebral blood flow is expected after aerobic exercise than stretching.

To address Objective 3, we will ask participants to complete language testing and a 3rd MRI scan after completing the intervention. We expect greater increases in cerebral blood flow, brain connectivity, and task-related activation in the AET condition compared to the stretching condition. These increases are expected to be most evident in areas supporting phonology and orthography-to-phonology mapping. The increased cerebral circulation and brain activity are expected to predict reading and other language outcome gains.

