### Semantic      Phonological      Orthographic

|                |                |                |
|----------------|----------------|----------------|
| goose          | gake           | beff      ffeb |
| lamb      swan | daik      jeak |                |

Figure 1. Example trials in the behavioral task administered to patients.

Treiman 1997). Patients will also complete a reading aloud task, in which they will be asked to read single words, with varying lexical characteristics, as well as pseudowords.

- Patient demographics will be collected using a self-report questionnaire. The PI will assist patients in completing the questionnaire and where necessary will contact family members for additional information.
- Participants will complete the Reading Comprehension Battery for Aphasia (RCBA-2nd edition), and, additionally, will complete will include the Western Aphasia Battery, Revised (WAB-R) (Kertesz, 2007), the Philadelphia Naming Test (PNT) (Walkera and Schwartz, 2012), and self-reported ratings of language disability from the Comprehensive Aphasia Test Disability Questionnaire (CAT-DQ) (Swinburn et al., 2004) .
- We will also assess depression via the Geriatric Depression Scale (Yesavage et al., 1982) (5 min), spatial neglect via the Behavioral Inattention Test-conventional(Halligan et al., 1990) (15 min), and screen for other cognitive deficits using the Oxford Cognitive Screen (OCS) (Demeyere et al., 2015) (1 hour). If found different between conditions, these tests will be used as covariates when examining the effects of intervention on behavioral and neural outcomes. A 10-meter walk test (Moore et al., 2018) and a 6-min walk test (Kosak and Smith, 2005) will be administered to measure the impact of the AET and stretching interventions on mobility (gait speed and walking distance).

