### 2. Participant Status Form

| Patient ID | Consent Date | Baseline Assessment (T0) Date | Treatment Completion Date | Immediate Follow-Up (T1) Date | One-month Follow-Up (T2) Date | Three-month Follow-Up (T3) Date | Reason for not completing the study |
|------------|--------------|-------------------------------|---------------------------|-------------------------------|-------------------------------|---------------------------------|-------------------------------------|
|            |              |                               |                           |                               |                               |                                 |                                     |
|            |              |                               |                           |                               |                               |                                 |                                     |
|            |              |                               |                           |                               |                               |                                 |                                     |
|            |              |                               |                           |                               |                               |                                 |                                     |

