## C. Analysis

All variables will be examined for outliers and appropriate strategies will be instituted if problems are identified. AET+PMT and Stretching+PMT will be compared on demographic and baseline variables (including baseline hypoperfusion) using two-sample t tests, Chi-square, or

equivalent non-parametric tests, as appropriate. Effect sizes (ES) will be calculated for all primary and secondary analyses. As recommended by Hahn (Hahn, 2012) for active control trials, we will conduct both intent-to-treat and per-protocol analyses and conclude AET+PMT superiority on the primary outcomes if both analyses support it. Per-protocol analyses will be conducted in those completing follow-up testing and in those who demonstrated good adherence and compliance. We will define adherence/compliance as completing at least 34 of the 40 possible treatment sessions as prescribed. This approximates the 85% adherence guideline for internal validity for RCTs based on the Physiotherapy Evidence Database (PEDro) scale. (Sherrington et al., 2000) Should attrition exceed expectations, we will use two-sample t-tests, Chi-square tests, or non-parametric equivalents to compare all baseline variables between subjects who remain in the study and those who drop out. Further specific analyses are described below.

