#### Univariate analyses:

*Behavioral data:* To measure the impact of treatment we will use a 2x2 repeated measures design assessing whether participants in the AET+PMT condition improve more from baseline to outcome than those in the Stretching+PMT condition. The reading tests (RCBA, reading aloud, touchscreen tests) will serve as primary outcomes and other language tests (WAB-R, PNT, CAT-DQ) as secondary outcomes. Improvement would be indicated by a significant condition by session interaction. We will also evaluate the within-subjects effect of PMT on reading improvement (post-treatment > baseline).

*Cerebral Blood Flow (CBF) data:* To examine the immediate effect of aerobic exercise on cerebral hemodynamics we will compare CBF measured with Arterial Spin Labeling (ASL) scans (used to measure cerebral circulation) at baseline (T1) with CBF measured after 20 min of moderate to vigorous intensity aerobic exercise (or 20 min of light stretching, T2).

ASL provides a non-invasive absolute (mL (blood volume)/100g (tissue volume)/min (time)) measure of CBF, that is suitable even for patients who may have impaired kidney function and cannot undergo contrast-based perfusion MRI (Zaharchuk, 2014). In ASL, water molecules are labeled with a magnetic pulse before they enter the brain through the arterial blood supply. The effect of labeling can be quantified by characterizing the interaction of blood flow and label decay. (Detre et al., 1998, 2012) Thus, ASL will be used to provide a measure of CBF changes as a function of AET. It is well known that stroke and cardiovascular disease can cause deficits in temporal dynamics of blood flow (Roc et al., 2006; Treger et al., 2007). Furthermore, Altamura et al. (Altamura et al., 2009) reported that delays in the hemodynamic signal are associated with worsened cerebral autoregulation (maintenance of constant blood flow despite changes in arterial blood pressure). For this reason, in addition to changes to regional and global CBF, we will evaluate the spatial coefficient of variation (sCoV) in the ASL signal as an indirect measure of arterial transit time, as proposed in Mutsaerts et al. (Mutsaerts et al., 2017), because prolonged transit times lead to proportion of the ASL signal remaining in conduit arteries at the time of

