analysis, functional scans will be aligned to participants' high-resolution T1-weighted images and to MNI152 standard space using nonlinear registration with lesion weighting (Andersson et al., 2007; Jenkinson et al., 2002). Preprocessing will include robust motion correction carried out using XCPEngine (Ciric et al., 2017), which allows implementation of different schemes of motion correction, including ICA-AROMA (Pruim et al., 2015), shown to yield high network identifiability and low connection-distance dependence. We will further remove lesion-driven artifacts by inspecting individual-level independent variance components that spatially overlap with the lesion and removing them from analyses (Yourganov et al., 2018). We will extract timeseries data from the Gordon atlas ROI (Gordon et al., 2016) and conduct geodesic DS clustering on the dynamic FC matrices. We will then compute one geodesic reference connectome per resulting cluster and convert the FC into a vector by computing the geodesic distance of each FC matrix from each cluster's reference connectome. These vector representations will be used as input features to classify different MRI sessions (T1 vs. T2 (Aim 2) and T1 vs. T3 (Aim 3)) for each condition. As a final step, we will perform sensitivity analyses to validate a subset of features contributing most to classification accuracy. These features will represent unique FC patterns which highlight the changes across testing sessions (T1 vs. T2) and conditions (AET+PMT, Stretching+PMT). Using similar methods in our pilot study, we found widespread treatment-induced increases in rsFC in a subset of 94 Gordon ROI that spatially overlap with a reading network mask derived from the Neurosynth database (Yarkoni et al., 2011)

Additionally, there may be individual variability in the response to treatment. We will explore the role of individual factors on functional improvement during treatment by fitting a mixed linear effects model (MLM) to the data with participants' intercepts and slopes as random effects. Modeling individual variability via the MLM will allow us greater sensitivity in detecting treatment effects.

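### The primary two-wave interaction test and the imbalance-triggered covariate rule give up precision that pre-specified adjustment for baseline and fixed covariates would keep at almost no cost

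*Protocol*

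**What the plan says.** - **Primary test.** Under C. Analysis, Univariate analyses, for the behavioural outcomes: "we will use a 2x2 repeated measures design assessing whether participants in the AET+PMT condition improve more from baseline to outcome". The decision criterion follows: "Improvement would be indicated by a significant condition by session interaction".
- **Occasions.** Section 2, Objectives, has the language outcomes measured "using standardized and experimental tasks administered before and after the full course of treatment", which is two occasions.
- **Covariates.** Under B. Research Procedures, after listing the depression scale, the neglect test and the cognitive screen: "If found different between conditions, these tests will be used as covariates when examining the effects of intervention on behavioral and neural outcomes". No threshold is given for a difference.
- **Baseline comparison.** Under C. Analysis the two arms "will be compared on demographic and baseline variables (including baseline hypoperfusion) using two-sample t tests, Chi-square, or" non-parametric equivalents. These are significance tests between randomised arms, and they could feed the covariate rule.
- **Analysis sets.** C. Analysis plans intent-to-treat and per-protocol analyses and requires both to support superiority. Only the per-protocol set is restricted to people with follow-up testing.
- **Exploratory model.** At the end of Multivariate analyses, individual variability is to be explored by "fitting a mixed linear effects model (MLM) to the data with participants' intercepts and slopes as random effects", with a claim of better sensitivity to treatment effects.

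**The concern.** This is not detail left to a later plan. The protocol itself fixes a model and a covariate rule, and both are weak choices.

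In a randomised comparison any baseline difference between arms is due to chance. A covariate earns its place by its relation to the outcome, not by a between-arm test. A rule that waits for imbalance lets the data pick the model and usually leaves a useful covariate out. The change-score test uses the baseline score, but with its coefficient fixed at 1 instead of estimated.

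At stake is power in a trial of 100 people, using variables that will be collected anyway.

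**Working it through.** **Inputs.** The protocol gives a total of 100 participants and two behavioural occasions. It gives no alpha, power, effect size, standard deviation, baseline-outcome correlation r, dropout rate or allocation ratio, so there is no stated figure to reproduce. Assumed here: 50 per arm, two-sided alpha 0.05, equal SDs at both occasions (set to 1), and a range for r.

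**Step 1: the interaction is a change-score test.** With two occasions the interaction contrast is (mean outcome − mean baseline) in one arm minus the same difference in the other. That is a two-sample comparison of change.
- Variance of change: 2(1 − r).
- Residual variance after baseline adjustment (ANCOVA): 1 − r².
- Ratio, adjusted to change: (1 − r²) / [2(1 − r)] = (1 + r)/2.

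The effect detectable with 80% power is (1.96 + 0.842) × √(2v/50), with v either variance. At r = 0.7 the change analysis gives 2.802 × √(2 × 0.60/50) = 0.434 SD, and ANCOVA gives 2.802 × √(2 × 0.51/50) = 0.400 SD.

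| Assumed r | Variance ratio | Variance saved | Detectable effect, change | Detectable effect, ANCOVA | ANCOVA power where change has 80% |
|---|---|---|---|---|---|
| 0.5 | 0.75 | 25% | 0.560 | 0.485 | 90% |
| 0.7 | 0.85 | 15% | 0.434 | 0.400 | 86% |
| 0.8 | 0.90 | 10% | 0.354 | 0.336 | 84% |
| 0.9 | 0.95 | 5% | 0.251 | 0.244 | 82% |

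**Step 2: how often the trigger fires by chance.** For three independent screens tested at 0.05: 1 − 0.95³ = 0.143, about 14% of trials.

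**Step 3: what the trigger achieves.** A simulation of 6,000 trials per scenario used r = 0.7, a true effect of 0.434 SD, and three covariates. One of these explained 16% of the outcome variance left after baseline; the other two explained none.

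| Analysis | Type I error | Power |
|---|---|---|
| Change score | 4.9% | 79% |
| Change score with triggered covariates | 4.2% | 79% |
| ANCOVA on baseline | 4.7% | 85% |
| ANCOVA plus the three covariates, fixed | 4.8% | 89% |

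A second simulation (20,000 trials) isolated a single covariate with a true effect of 0.5 SD. A separate run of 40,000 trials agreed within one percentage point.

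| Assumed covariate R² | Power, triggered | Power, fixed in advance |
|---|---|---|
| 0.1 | 70% | 74% |
| 0.2 | 70% | 78% |
| 0.4 | 71% | 89% |

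Never adjusting gave 70%. Type I error of the triggered rule was 3.8% at R² = 0.4.

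**Step 4: random intercept and slope with two scores.** Let s0, s1 and s01 be the intercept variance, slope variance and their covariance, and se the residual variance. The observable moments are V0 = s0 + se, C = s0 + s01 and V1 = s0 + 2s01 + s1 + se: three moments for four parameters (rank 3). For example, (s0, s01, s1, se) = (0.7, 0, 0, 0.3) and (0.9, −0.2, 0.4, 0.1) both give V0 = V1 = 1 and C = 0.7, so the data cannot tell them apart. With three occasions there are six moments and the rank is 4, so the model is identified.

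**The case against.** Several stronger readings are tempting, and the protocol does not support them.

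- **Baseline is thrown away.** It is not. A change score uses every baseline value, only inefficiently. If r is near 0.9 the loss is about 5%, and the protocol gives no r.
- **People without an outcome visit are dropped.** A reader might infer this from a classical two-occasion analysis of variance. But the text plans intent-to-treat, limits only the per-protocol set to completers, and does not name a complete-pairs method for the behavioural data. A likelihood-based repeated measures model would keep them, and handling of missing outcomes may stand in an analysis plan not shown.
- **The trigger inflates false positives.** The simulations show the reverse: type I error of about 4%. The cost is power.
- **The trial's fall-back model will fail.** The mixed model is offered as exploration, not as a back-up. It is described as fitted to the data generally, and the MRI measures have three occasions. The DSMB status form also has a column "One-month Follow-Up (T2) Date" and a three-month one, though the procedures describe no such visits. Even with two scores, only the split of the variance is unidentified; the condition-by-time effect can still be estimated. In one simulation with 20% missing outcomes and r = 0.7, a model with that covariance gave a slightly smaller variance than complete-case change (0.0291 against 0.0301).

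It is also fair to say that the largest gains need a strongly prognostic covariate. In the three-covariate simulation, baseline adjustment moved power from 79% to 85%, and the fixed covariates added about four points. What remains is that the chosen test is less efficient than a readily available one, and that the trigger brings almost nothing.

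**Conclusion.** The point holds in this limited form. The primary test has 2/(1+r) times the variance of a baseline-adjusted analysis: 1.33, 1.18, 1.11 and 1.05 times at r = 0.5, 0.7, 0.8 and 0.9. The covariate rule makes the final model depend on chance imbalance and yields almost no power over never adjusting, while pre-specified adjustment gains power as the covariate's R² rises.

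This is avoidable inefficiency, not a threat to validity. The sizes rest on assumed alpha, 1:1 allocation, equal SDs, r, R², effect size and a 0.05 trigger, none of which the protocol states. The random-slope point is minor: it applies to summary scores taken twice, and there it concerns the variance components and not the treatment effect.

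**What to change.** - Make the primary model the outcome score on arm, its own baseline score and a short fixed covariate list, used whatever the observed balance. Name the list now from data already collected, for example age, time since stroke and baseline aphasia severity.
- Delete the rule that adds covariates only after a between-arm difference, and do not let baseline significance tests decide the model.
- Consider fitting this as a baseline-constrained longitudinal model. It would keep randomised participants who have no outcome visit, in line with the intent-to-treat claim.
- Limit random slopes to item-level data or to outcomes with three or more occasions, such as the MRI measures. For language summary scores taken twice, explore individual response through arm-by-baseline-factor interactions. State whether the follow-ups on the status form are collected.

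The cost is analysis wording and a few degrees of freedom. No new data are needed.

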- **Potential risks** to patients may include fatigue from completing neuropsychological testing and participating in MRI sessions. To protect against such risks, behavioral tests will be targeted to last one hour (but will not exceed 2) and will be administered at a time when the patient is not involved in therapy. MRI scanning will take place in the same building as inpatient care requiring minimum transportation and will last no longer than 1 hour. There are no known significant risks or side effects associated with MRI scans when all scanning parameters remain within FDA guidelines and when all participants with contraindications for MRI are excluded. The study will adhere to the FDA regulations and to the inclusion and exclusion criteria. Potential discomforts include feelings of claustrophobia and discomforts associated with considerable background noise generated by the MRI scanner (approximately 120 dB peak SPL). Participants will be screened for prior history of severe claustrophobia and during the scan all participants will be wearing earplugs to protect their hearing. Moderate intensity exercise may be associated with an increased risk of musculoskeletal injury, irregular heart rhythms, and shortness of breath. To safeguard against these risks, we will exclude participants who have moderate to high-risk contraindications for aerobic exercise. Additionally, all aerobic training sessions will be supervised by trained staff. Heart rate will be monitored continuously to ensure that the participants stay within the prescribed exercise intensity limits. The proposed aerobic exercise intervention (5 days/week of 20 mins of moderate intensity, 60-70% of heart rate range) approximates public health guidelines for aerobic activity (i.e., 150 mins/week of moderate or 75 mins/week of vigorous activity). Furthermore, numerous studies demonstrated beneficial impact of exercise on physical and cognitive metrics (Lefferts et al., 2019; Mayer et al., 2021; Northey et al., 2018; Zheng et al., 2016)

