- They will undergo 3 MRIs, including structural, perfusion, and functional sequences. Each scan will last approximately 50 minutes. The results of the scans will be used to determine the size and location of the stroke lesion, and the impact of treatment on cerebral blood flow and function. Participants will undergo 40 sessions of treatments (2 hours each). The treatment will start with 20 minutes of aerobic exercise (cycling) or stretching preceded and followed by 5 minutes of warm up and cool down. Participants' heart rate will be monitored continuously, and those undergoing aerobic exercise will be asked to exercise at a heart rate equal to 60-70% of their individual maximal heart rate (i.e., moderate intensity). Aerobic exercise will be supervised by a senior scientist with physical therapy and exercise research expertise ([name]). The exercise will be followed by 1,5 hours of reading therapy (Phono-motor treatment) (Kendall et al., 2019). The treatment fidelity will be monitored by the co-I, [name], who will review randomly selected treatment session videos at a rate of ~1 video/week/participant.
- Some participants may not complete all sessions according to the proposed schedule due to unforeseen circumstances (such as participant or staff illness, transportation problems, etc.) or because of holidays or other commitments. Efforts will be made to reschedule missed sessions as close to the original proposed dates as possible. The total length of the intervention period may also be extended if needed to provide time to reschedule missed sessions.
- In addition to assessing the rate of perceived exertion during each 5-minute exercise interval, we will ask participants to rate their enjoyment, willingness to continue to engage in the exercise program, and difficulty adhering to the program at the end of each

exercise session. We will also prompt participants for free form comments about their experience in the program.

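### The cycling intensity, which defines the trial's only between-arm contrast, is stated with two different heart-rate bases and two intensity labels

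*Protocol*

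**What the plan says.** Both arms receive the same phono-motor reading therapy. They differ only in what comes before it: cycling or light stretching.

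**Heart-rate target**
- Protocol section 5B (Research Procedures): the aerobic arm is to "exercise at a heart rate equal to 60-70% of their individual maximal heart rate (i.e., moderate intensity".
- Protocol section 5A (Participants, potential risks): the same intervention is "5 days/week of 20 mins of moderate intensity, 60-70% of heart rate range". This follows directly on the statement that continuous heart-rate monitoring will keep participants inside their prescribed limits. The term range is not defined.

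**Intensity label**
- Section 2 (Objectives): "20 minutes of moderate intensity aerobic exercise in the form of stationary bike cycling". Sections 5A and 5B also say moderate.
- Section 5C (Analysis, cerebral blood flow): "CBF measured after 20 min of moderate to vigorous intensity aerobic exercise". Section 2 places that second scan after the first exercise session.

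**Schedule and adherence**
- Section 2: "40, 2-hour intervention sessions administered 3-5 times per week for 8-10 weeks".
- Section 5B lets the intervention period be lengthened so that missed sessions can be rescheduled.
- Section 5C defines adherence as "completing at least 34 of the 40 possible treatment sessions as prescribed". It declares superiority only when the intent-to-treat and per-protocol analyses both support it.

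**The concern.** The same percentages are applied to two different quantities, and both results are called moderate. A percentage of maximal rate and a percentage of the span between resting and maximal rate are different prescriptions. A third section then describes the exercise before the second scan with a label that reaches into vigorous intensity.

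Three things are at stake:

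- **The experimental dose.** Staff working from different sections could hold participants at different heart rates, so the effect the trial estimates would not belong to one defined intervention. Objective 2 rests on the single session whose label differs.
- **The safety limit.** The risk text offers heart-rate monitoring within prescribed limits as a safeguard. The only figure given there is not the one in the procedures.
- **The primary conclusion.** If completing a session as prescribed includes its intensity, one session can comply under one section and fail under the other. The target applies only to the cycling arm, so the choice of reading would alter per-protocol membership in that arm alone.

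**Working it through.** **Figures that agree.** 40 sessions x 1.5 h = 60 h of reading therapy, as stated. 34/40 = 85%, as stated.

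**Heart-rate bands.** Let M be maximal and R resting heart rate. The protocol gives neither, so the values below are assumptions. Range is read as M - R, which is also an assumption.

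- Band A (Research Procedures): 0.60M to 0.70M.
- Band B (risk text): R + 0.60(M - R) to R + 0.70(M - R), that is 0.60M + 0.40R to 0.70M + 0.30R.
- Gap from the top of A to the bottom of B: 0.60M + 0.40R - 0.70M = 0.40R - 0.10M. This is positive when R > 0.25M.
- Difference between the two upper limits: 0.30R, whether or not the bands overlap.

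| M (assumed) | R (assumed) | Band A, bpm | Band B, bpm | Gap, bpm |
|---|---|---|---|---|
| 120 | 60 | 72-84 | 96-102 | 12 |
| 150 | 70 | 90-105 | 118-126 | 13 |
| 160 | 60 | 96-112 | 120-130 | 8 |
| 160 | 40 | 96-112 | 112-124 | 0 (touch) |
| 180 | 40 | 108-126 | 124-138 | -2 (overlap) |
| 202 | 50 | 121.2-141.4 | 141.2-156.4 | -0.2 (overlap) |

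At 150/70, band A expressed as a share of the range is (90 - 70)/80 = 25% to (105 - 70)/80 = 44%, against the 60-70% in the risk text. The upper limits differ by 0.30 x 70 = 21 bpm. In the overlapping 180/40 case they still differ by 0.30 x 40 = 12 bpm.

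**Labels.** Sections 2, 5A and 5B say moderate. Section 5C says moderate to vigorous for the exercise before the second scan. No text explains the difference.

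**Schedule.** Sessions = frequency x weeks:

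| Per week | 8 weeks | 9 weeks | 10 weeks |
|---|---|---|---|
| 3 | 24 | 27 | 30 |
| 4 | 32 | 36 | 40 |
| 5 | 40 | 45 | 50 |

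Forty sessions within 10 weeks need an average of at least 40/10 = 4 per week. At 3 per week throughout, 40 sessions take 40/3 = 13.3 weeks and 34 sessions take 34/3 = 11.3 weeks, both beyond the stated window.

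**The case against.** **On heart rate.** Only Research Procedures instructs participants on a target. The figure in the risk text is a parenthesis comparing the intervention with public health guidance, and the wording in the blood-flow analysis is descriptive. Range might be loose wording for maximal rate. Exercise is prescribed individually, supervised by a specialist and monitored continuously. This limits the claim: staff could apply different targets, but the document does not show that they would. It does not remove the contradiction. The risk text gives its figure in the same place as the monitoring limits, leaves the term undefined, and the individual prescription names no formula.

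A reader might infer that the two bands can never coincide. That goes too far. Separation depends on reading range as maximal minus resting rate, and it fails when resting rate is 25% of maximal or less.

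**On the schedule.** A reader might infer that the stated frequency cannot deliver 40 sessions. It can: 4 per week for 10 weeks and 5 per week for 8 weeks both give 40, and the 5 days a week in the risk text lies within the stated 3-5.

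A reader might also infer that someone on 3 sessions a week for 10 weeks is non-adherent by design. The documents do not support this. The total of 40 is fixed in several sections, and none allows a planned 30-session course. The provision to lengthen the period means that 10 weeks is not a hard stop for someone who misses sessions. That provision covers missed sessions only, so it does not make a course planned at 3 per week fit the window.

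**Conclusion.** The intensity is wrong as written. Two sections apply 60-70% to different quantities, and a third uses a different intensity label, for the component that alone separates the arms. That much needs no assumption. The size does: if range means maximal minus resting rate, the bands are disjoint for almost all plausible resting rates (13 bpm apart at an assumed 150/70), and the upper limits differ by 30% of the resting rate. If range means something else, the target in the risk text is undefined and still needs correcting.

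The effect on the per-protocol set, and so on the superiority conclusion, assumes that completing a session as prescribed includes intensity. If only attendance counts, that effect falls away, but the text does not say so.

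The schedule is a minor wording point. Only average frequencies below 4 per week fall short of 40 sessions within 10 weeks.

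**What to change.** The sponsor should reconcile section 2, the risk text in 5A, the procedures in 5B, and the adherence and blood-flow text in 5C:

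- State one heart-rate definition with its formula, and one intensity label. Use them identically in the risk, procedure, blood-flow analysis and adherence text.
- Say whether completing a session as prescribed covers intensity or attendance alone.
- Make the stated frequency and duration consistent with 40 sessions and with the 34-session threshold.
- Recruitment was scheduled from summer 2024, so if participants have already been treated, record which target was in force.

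Which values apply is for the clinical team. The cost is a wording amendment and a staff instruction. No extra participants or assessments are needed.
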